#### 7.2.2. Methods

Following the characteristics of the CBPR approach, this proposed project will have the following four stages:

##### Stage 1: Establishing the Collaboration Platform with Local Community Stakeholders

We will officially invite target NGOs, middle schools, and companies/businesses to join our project as research partners. They will be involved in forming the collaboration platform for the project. Collaboration will occur at various levels. Working groups consisting of centre-in-charge/frontline workers will be designated by their managers. They will work on the design, implementation and evaluation of the intervention through the administration of questionnaires, participation in process evaluations, the production and dissemination of professional toolkits and the promotion of educational programmes to the public. Once the collaboration platform is formed, steering committee meetings will be held every 3 months to monitor the progress of the intervention programmes, discuss the challenges and barriers encountered in the implementation of the programmes, and identify solutions for any problems encountered.

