Sample size: As a cluster RCT, the randomization is conducted in the cluster level. In our study, each cluster is a group of participants recruited by the same research partner. In our study, based on our simulation modelling [32], a 20% increase in the vaccination rate could have significant social benefit. With conventional assumptions of a two-sided 5% significance level and assuming an intra-cluster correlation of 0.01, we would have 86% power to detect a difference of 20% if there are 50 participants in each cluster and 8 clusters in each sector [33]. Thereby 3 sectors will have 3 × 8 = 24 clusters and 1200 participants in total. For each sector, 8 clusters (400 participants) will be evenly divided into either the intervention group or the control group. When we used the same method to calculate the sample size for detecting 20% difference in the percentage of early testing (another primary outcome), the sample size was smaller than the previous one. We thereby consider the former one as our final sample size, as it could ensure the power of the study.

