##### Stage 2: Pilot Study and Capacity Building for Research Partners: Train-the-Trainer (TTT) Workshops

Design and setting: stage 2 includes two parts, a pilot study for participants and a mixed-methods study for the research partners. The purpose of the pilot study is to determine the most optimal components of the ‘core intervention package’ which will be delivered in the formal cluster RCT. We will conduct a single arm pre-post experimental study among 50 participants in the community, to assess the effect of intervention components and assessing whether the intervention component effects vary with the individual’s current context. The pilot study will last for 4 months. The evidence obtained from the pilot study will be introduced to the workshop participants, to facilitate the design and implementation of their own programmes later. The research partners will designate their centre-in-charge/ frontline staff to attend the TTT workshops. Each collaborator will designate 2–3 staff members. We expect that at least 48 individuals will attend the training workshops. Two rounds of workshops will be conducted within 5 months. The staff will be divided equally into the two rounds of training. 

Training content: The workshops will have 3 sessions, and each session lasts for 2 h. The content will include: (1) basic cluster RCT design and CBPR knowledge; (2) key knowledge of COVID-19 prevention and protection, and the benefits of early testing and vaccination; (3) the use of the PROCEDE-PROCEED model [34] to assess the health needs and develop the community-based education programmes; (4) the use of a knowledge-attitude-practice (KAP) model [35] to evaluate the effectiveness of the health education intervention; (5) the content of the core intervention package; and (6) the suggested channels and approaches for intervention implementation. 

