##### Stage 3: Implementing the Community-Based Health Education Programmes

Design and setting: stage 3 is a multicentre cluster RCT. The intervention programmes will be implemented by the research partners. 

Randomisation and concealment: The participants recruited by one research partner will be considered as one cluster. A research assistant will randomly assign the clusters from the NGOs, Schools, and Companies to either the intervention group or the control group, respectively. Concealment of the allocation sequence to the investigators will be done until assignment occurs. After allocation, there will be four clusters in both the intervention and control groups from the NGOs, schools and companies, respectively. This will result in 3 × 4 = 12 clusters for each group (intervention/control). An active wait-list control group will be used instead of a standard control group to help motivate the collaborators to implement the programme and to avoid a high participant dropout rate. Intervention: The core intervention package will potentially include the following four components. (1) A manual of self-protection against COVID-19 infection. The main content will include hand washing, mask wearing and social distancing guidelines. (2) Early testing. Participants will be trained on how to recognize the early symptoms of COVID-19 and appropriate practice to take in a response, and they will be provided with testing resources. The COVID-19 Rapid Antigen Test (RAT) will be provided to participants as an incentive to facilitate self-testing at home. This RAT is a lateral-flow immunoassay designed for the qualitative detection of SARS-CoV-2 antigens in nasal swab samples. (3) Knowledge of vaccines and their benefits and resources for vaccination. (4) Post-vaccination follow-up. Participants will be trained on how to recognise vaccine side effects and to provide further protection measures, and they will be provided with resources for consultation and treatment. The research partners will design the community-based education programmes (based on the core intervention) after the TTT workshop. They will be required to submit a brief standardized proposal to the academic investigators for review and approval, to ensure that all intervention programmes have the same core intervention contents and can be implemented appropriately. The development and implementation of the intervention will follow the procedures outlined in the PROCEDE-PROCEED model (Figure 2). Research partners will be able to use any reasonable strategies, such as social media platforms, information technology, posters, leaflets, and videos, to implement the programmes. Each programme will last for 3 months. The active wait-list control group will undergo parallel assessment at the same time points as the intervention group, while the core intervention contents will be delivered after 3 months. We expect that the 24 intervention programmes will be completed within 2 years. Evaluation: Evaluations will be conducted at baseline (T_0_), middle term (T_1_, 1.5 months), and at the end of the trial (T_2_, 3 months). Participants’ knowledge, attitudes and behaviours towards COVID-19 prevention will be evaluated using a self-designed questionnaire, based on the KAP model. In addition, a process evaluation that determines whether the programme is being implemented as intended will be performed as follows. Every month, the academic investigators and the collaborators will review the progress of each programme together. Information on the attendance rate of each programme and feedback from program participants and research partners will also be evaluated qualitatively. A flow chart of the all the data collection steps is shown in Figure 3.

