
##### Stage 4: Health education model enhancement and promotion

An agent-based simulation model that considers human mobility in HK will be developed [36]. The model will be trained using data from the 24 community-based intervention programmes, to establish the most optimal community-based health education model(s) for COVID-19 prevention. We assume different intervention programmes will cause different changes in the vaccine uptake patterns among participants. Each intervention programme’s result (e.g., the vaccine uptake number) will be collected for comparison purposes. Then, the programme with maximal vaccine uptake and minimal healthcare requirements (e.g., number of infections detected) will be chosen as the most optimal strategy. Once the simulation modelling is completed, a toolkit book that contains (1) training workshop content and (2) details on the implementation and assessment of the most optimal health education model(s) will be produced and disseminated to additional NGOs, companies and schools. A health education pamphlet containing relevant COVID-19 information and the successful experiences of our health education programmes will be disseminated to the public via the research partners within one year. We expect that 200 NGOs, companies and schools will be approached, and 20,000 HK residents will receive the pamphlets. In addition, several press conferences will be held to share our findings and experiences with the public.

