#### 7.2.3. Data Type, Data Processing and Analysis

Stage 1 will involve administrative processes for building the collaboration platform. No data will be collected at this stage. During Stage 2, quantitative data will be collected using a self-administered questionnaire. Qualitative data will also be collected through focus group interviews. The transcription of data will be done after the focus group interviews. During Stage 3, all data generated will be quantitative. The primary outcomes will be vaccination rates. It will be calculated as the number of participants who have been vaccinated over the total number of participants. Each participant’s vaccine uptake will be recorded by asking the participants to provide their COVID-19 vaccination record in the Vaccine Pass, or the paper vaccine certificate delivered by the HK government. The secondary outcomes will be the amount and frequency of early testing, the levels of acceptability for vaccination and early testing, and the changes in knowledge, attitude and behaviour towards COVID-19 protection and prevention, as determined by a self-administered questionnaire. The questionnaires will be designed based on the KAP model. The validity and reliability of the questionnaires will be assessed in advance.

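### Study 1: partner staff who design and deliver the programmes also appear to administer the evaluation questionnaires, which exposes the self-reported outcomes to avoidable reporting bias that can differ by arm

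*Protocol article*

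**What the plan says.** All references are to Study 1 (section 7) of the Protocol article, unless stated.

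- **Who evaluates.** Section 7.2.2, Stage 1: "Working groups consisting of centre-in-charge/frontline workers will be designated by their managers". The next sentence gives these groups their tasks: "They will work on the design, implementation and evaluation of the intervention through the administration of questionnaires". Taking part in process evaluations is listed there as a separate task.
- **Who designs and delivers.** Stage 3: "The intervention programmes will be implemented by the research partners" and "The research partners will design the community-based education programmes (based on the core intervention) after the TTT workshop".
- **Training.** The Stage 2 workshops teach partner staff "the use of a knowledge-attitude-practice (KAP) model [35] to evaluate the effectiveness of the health education intervention". KAP is also the basis of the Stage 3 participant questionnaire.
- **Whom they serve.** Section 7.2.1: "each cluster is a group of participants recruited by the same research partner". Partners are NGOs, employers and school teachers.
- **How outcomes are obtained.** Section 7.2.3 takes vaccination from the Vaccine Pass or paper certificate. Early testing, acceptability and KAP change are secondary outcomes, "as determined by a self-administered questionnaire". The sample-size paragraph in section 7.2.1, however, calls early testing another primary outcome.
- **Timing and blinding.** Assessments are at baseline, 1.5 months and 3 months in both arms, and the wait-list arm receives the content after 3 months. Allocation is concealed until assignment. No independent or blinded outcome collection is stated for Study 1.

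**The concern.** Read together, these statements let the people who build and run a programme also handle the forms that judge it, and the respondents are their own employees, pupils or service users. Partners stand in this relation to participants in both arms. The difference appears after baseline: at T1 and T2 an intervention participant returns the form to someone who has just taught the recommended behaviour, and a wait-list participant does not.

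A reporting shift of this kind would enter the between-group change from baseline directly. Neither the intention-to-treat principle nor the linear mixed models in section 7.2.3 can separate it from a true effect. It matters most for early testing, because one section treats that outcome as primary.

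**Working it through.** **Step 1. Does the text assign the role?** Stage 1 links evaluation of the intervention to administering questionnaires and lists process evaluation separately. Stage 2 trains the same staff to evaluate effectiveness with KAP, and the Stage 3 outcome form is a KAP questionnaire. Together these point to the outcome forms. Stage 1 does not name the T0, T1 or T2 forms, so this remains an inference.

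**Step 2. Which outcomes are exposed?** Vaccination is document-verified and largely protected. Early testing, acceptability, knowledge, attitude and behaviour are reported by the participant and exposed.

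**Step 3. How sensitive is the comparison to a one-arm shift?** The article gives no figure for reporting bias, so there is none to reproduce. Inputs from the article: ICC 0.01, 50 participants per cluster, two-sided 5% level (section 7.2.1) and 12 clusters per arm (Stage 3). The ICC was chosen for the vaccination rate; applying it to KAP scores is an assumption.

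- Participants per arm: 12 × 50 = 600.
- Design effect: 1 + (50 − 1) × 0.01 = 1.49.
- Standard error of a standardised mean difference: √(2 × 1.49 / 600) = 0.0705.
- Degrees of freedom at cluster level: 24 − 2 = 22, critical t = 2.074.

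With a true effect of zero and intervention-arm reports shifted by an assumed amount b, the noncentrality is b / 0.0705, and the chance of a significant result is:

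| Assumed shift b | Noncentrality | ICC 0.01 | ICC 0.05 (assumed; SE 0.107) |
|---|---|---|---|
| 0 | 0 | 5% | 5% |
| 0.1 SD | 1.42 | 27% | 14% |
| 0.2 SD | 2.84 | 77% | 43% |
| 0.3 SD | 4.26 | 98% | 76% |

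The noncentralities shown are for ICC 0.01. For ICC 0.05 the design effect is 1 + 49 × 0.05 = 3.45.

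**Step 4. The same check for a yes/no outcome such as early testing.** The effective number per arm is 600 / 1.49 = 402.7. For an assumed true rate p, the standard error is √{[p(1 − p) + (p + b)(1 − p − b)] / 402.7}. For p from 0.3 to 0.7 and a normal test, a 5-point shift gives a significant result favouring the intervention in about 30 to 36% of trials, and a 10-point shift in about 82 to 91%. With no shift this figure is 2.5%.

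The shifts are assumptions. The calculation shows how little differential reporting is needed to mislead; it does not show that such a shift will occur, or how much of it would come from partner handling.

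**The case against.** The case on the other side is substantial.

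- **The role is inferred.** Stage 1 is a general list of collaboration tasks, and its questionnaires could be for needs assessment. The paragraphs on outcome measurement do not name partners as administrators. This stands as a limit on certainty. Even so, tying questionnaires to evaluation of the intervention makes outcome forms the more natural reading.
- **The forms are self-completed.** Partners would at most hand out and collect them, so it goes too far to say that participants answer face to face to an employer or teacher. Section 13 also promises anonymity and confidentiality, limits data access to authorised personnel and holds collaborators to protecting data. These measures reduce the pressure. They do not say who distributes the forms or who can see them on return.
- **Who collects is balanced.** Control partners handle their own people's forms too, and knowledge items cannot be answered correctly out of politeness. So a reader should not infer that every self-reported outcome must be biased towards the intervention. The remaining asymmetry is that only intervention partners have delivered a programme by T1 and T2.
- **No contest is described.** A reader might infer from Stage 4 that partners compete to be picked as the best model. The article sets no contest or reward. Stage 4 selects "the programme with maximal vaccine uptake and minimal healthcare requirements" and draws on all 24 programmes, including the wait-list ones, so favourable KAP answers are not a stated criterion.
- **The arithmetic is not specific.** A shift of the same size from any source gives the same percentages, and some self-report bias is unavoidable in an unblinded education trial. This stands.
- **Partner involvement is the declared method, and form handling is often left to a fuller protocol.** True in general, but here the article states an allocation of roles; it does not merely omit a detail.

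**Conclusion.** The point holds in a limited form. The article gives partner staff who design and deliver the programmes a part in evaluating them by questionnaire, and it states no independent collection. The self-reported outcomes, including early testing with its unclear primary or secondary status, are therefore open to a reporting bias that can differ by arm. The documents do not support reading this as a threat to the vaccination result, or as a demonstrated bias.

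The size is unknown. The figures of about 27% and 77% rest on assumed shifts of 0.1 and 0.2 SD in one arm, the article's ICC of 0.01 carried over to KAP scores, and analysis of all 24 clusters; they fall to 14% and 43% at an assumed ICC of 0.05. Central collection would remove only the part caused by partner handling. This is a cheap improvement, best made before data collection because the bias cannot be repaired afterwards.

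**What to change.** Amend the Stage 1 and Stage 3 paragraphs of section 7.2.2 to state that:

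- the university team sends and collects the T0, T1 and T2 questionnaires directly, by personal link or sealed form;
- invitations and reminders are identical in both arms and follow the same schedule;
- partner staff do not see or collect individual answers;
- partners keep programme design, delivery and process evaluation, which preserves the participatory approach.

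If the Stage 1 questionnaires were never meant to be the outcome forms, one sentence saying so and naming who collects those forms would settle the point.

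The cost is protocol wording and a survey link or sealed forms. The downside is a possibly slightly lower response without on-site prompting, which equal central reminders can partly offset.

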##### Stage 2: Pilot Study and Capacity Building for Research Partners: Train-the-Trainer (TTT) Workshops

Design and setting: stage 2 includes two parts, a pilot study for participants and a mixed-methods study for the research partners. The purpose of the pilot study is to determine the most optimal components of the ‘core intervention package’ which will be delivered in the formal cluster RCT. We will conduct a single arm pre-post experimental study among 50 participants in the community, to assess the effect of intervention components and assessing whether the intervention component effects vary with the individual’s current context. The pilot study will last for 4 months. The evidence obtained from the pilot study will be introduced to the workshop participants, to facilitate the design and implementation of their own programmes later. The research partners will designate their centre-in-charge/ frontline staff to attend the TTT workshops. Each collaborator will designate 2–3 staff members. We expect that at least 48 individuals will attend the training workshops. Two rounds of workshops will be conducted within 5 months. The staff will be divided equally into the two rounds of training. 

Training content: The workshops will have 3 sessions, and each session lasts for 2 h. The content will include: (1) basic cluster RCT design and CBPR knowledge; (2) key knowledge of COVID-19 prevention and protection, and the benefits of early testing and vaccination; (3) the use of the PROCEDE-PROCEED model [34] to assess the health needs and develop the community-based education programmes; (4) the use of a knowledge-attitude-practice (KAP) model [35] to evaluate the effectiveness of the health education intervention; (5) the content of the core intervention package; and (6) the suggested channels and approaches for intervention implementation. 

Evaluation: Pre- and post-programme evaluations will be implemented. Before attending the workshop (T_0_), all participating staff will be required to complete a questionnaire asking about information related to the COVID-19 epidemic and the content of the training workshop, to evaluate their knowledge, attitude and intention to implement the community education programmes. Similar assessments will be performed soon after completion of the training workshop (T_1_) and after implementing the intervention programmes (T_2_). Furthermore, two focus group interviews will be conducted for twenty randomly selected trainees, to understand their views on the training workshop in terms of the content, method, materials, their level of satisfaction, experiences and views on implementing the education programmes, and suggestions for improvement.

##### Stage 3: Implementing the Community-Based Health Education Programmes

Design and setting: stage 3 is a multicentre cluster RCT. The intervention programmes will be implemented by the research partners. 

Randomisation and concealment: The participants recruited by one research partner will be considered as one cluster. A research assistant will randomly assign the clusters from the NGOs, Schools, and Companies to either the intervention group or the control group, respectively. Concealment of the allocation sequence to the investigators will be done until assignment occurs. After allocation, there will be four clusters in both the intervention and control groups from the NGOs, schools and companies, respectively. This will result in 3 × 4 = 12 clusters for each group (intervention/control). An active wait-list control group will be used instead of a standard control group to help motivate the collaborators to implement the programme and to avoid a high participant dropout rate. Intervention: The core intervention package will potentially include the following four components. (1) A manual of self-protection against COVID-19 infection. The main content will include hand washing, mask wearing and social distancing guidelines. (2) Early testing. Participants will be trained on how to recognize the early symptoms of COVID-19 and appropriate practice to take in a response, and they will be provided with testing resources. The COVID-19 Rapid Antigen Test (RAT) will be provided to participants as an incentive to facilitate self-testing at home. This RAT is a lateral-flow immunoassay designed for the qualitative detection of SARS-CoV-2 antigens in nasal swab samples. (3) Knowledge of vaccines and their benefits and resources for vaccination. (4) Post-vaccination follow-up. Participants will be trained on how to recognise vaccine side effects and to provide further protection measures, and they will be provided with resources for consultation and treatment. The research partners will design the community-based education programmes (based on the core intervention) after the TTT workshop. They will be required to submit a brief standardized proposal to the academic investigators for review and approval, to ensure that all intervention programmes have the same core intervention contents and can be implemented appropriately. The development and implementation of the intervention will follow the procedures outlined in the PROCEDE-PROCEED model (Figure 2). Research partners will be able to use any reasonable strategies, such as social media platforms, information technology, posters, leaflets, and videos, to implement the programmes. Each programme will last for 3 months. The active wait-list control group will undergo parallel assessment at the same time points as the intervention group, while the core intervention contents will be delivered after 3 months. We expect that the 24 intervention programmes will be completed within 2 years. Evaluation: Evaluations will be conducted at baseline (T_0_), middle term (T_1_, 1.5 months), and at the end of the trial (T_2_, 3 months). Participants’ knowledge, attitudes and behaviours towards COVID-19 prevention will be evaluated using a self-designed questionnaire, based on the KAP model. In addition, a process evaluation that determines whether the programme is being implemented as intended will be performed as follows. Every month, the academic investigators and the collaborators will review the progress of each programme together. Information on the attendance rate of each programme and feedback from program participants and research partners will also be evaluated qualitatively. A flow chart of the all the data collection steps is shown in Figure 3.
